### Data management

The Data Management Team, comprised of three statisticians and a data manager based at UCLA, provide ongoing analyses to the DSMB. In addition, they are responsible for ensuring successful randomization and data analyses.

A separate Assessment Team implements all assessments, follow-up interviews, and testing, and are responsible for quality data collection. Assessments are completed at a local storefront research study space. In addition to rapid diagnostic tests (RDT) for HIV and substance use at each scheduled assessment of outcomes, men in the two active intervention conditions are randomly tested for substance use while at soccer practices and games. At the outset of the study, the Assessment Team is blinded to intervention assignment, but participants often discuss their intervention activities during assessment interviews, causing unblinding over time. An Intervention Team, with a different supervisor, implements the soccer and vocational training interventions.

### Site

Cape Town is comprised of five major peri-urban settlements with formal and informal housing (shacks). Using charts of field workers of each community and street-intercept surveys of male residents, UCLA matched 24 neighborhoods based on the recency of migration, the density of bars (shebeens), the percentage of informal housing, and water on the premises. Buffer areas of at least 1 km or natural barriers, such as highways, railways, and rivers, separate each neighborhood. Contamination is further prevented by young men’s lifestyles, which lack readily available transport and are concentrated at kiosks, shebeens, and churches in their local areas. In each area, there is formal housing and vast areas of informal shacks. Each neighborhood contains approximately 450–600 households, including roughly 50 young men aged 18–29 years old. We have identified additional neighborhoods as back-up recruitment sites in case a natural disaster or political problem forces exclusion of any triad from our study. Following recruitment, the Data Management Team randomizes triads using R [47], and is not blinded to intervention assignment. Figure 3 summarizes the design of the cluster randomized controlled superiority trial and participant flow.

**Fig. 3 Fig3:**
[figure not shown]
Design of the cluster randomized controlled trial

### Recruitment

Recruiters underwent 1 month of training. Recruiters go dwelling-to-dwelling, randomly selecting the first household (by flipping a coin on a hardcopy neighborhood map, with a supervisor) to enter and then systematically approach houses in concentric circles until 50 young men aged 18–29 are identified per neighborhood and agree to participate, documenting all refusals. To be considered eligible, young men must be aged 18–29, have slept at least four nights per week in the household for the 2 months prior to recruitment, speak Xhosa or English, do not appear to be under the influence of any substances at the time of recruitment, and are able to understand the recruiter. Any potential participant who does not meet the five inclusion criteria defined above is considered ineligible and is not invited to participate in the study. We anticipate that it may take several household visits to contact and recruit the young men identified by their family members on recruitment visits. Since housing units are typically too small to provide confidential interviewing, we transport young men to a local storefront research study space to complete assessments. Recruiters remain in constant contact with drivers, so that when a potential participant expresses interest, the driver can both confirm that they live within the catchment area and transport them to the local storefront assessment center.

### Assessments

At the local storefront assessment center, trained interviewers obtain written voluntary informed consent and then administer a 1-h assessment, recording responses on mobile phones using a program designed by Mobenzi Technologies. Participants receive about ZAR 150 for their time to complete the interview (incentives are adjusted over time for inflation). Assessment data are coded with personal identification numbers (PIDs) and do not include any personally identifiable information. De-identified assessment data are available through a password-protected, cloud-based database and accessed by UCLA and Stellenbosch University for quality control and later analyses. Assessments are conducted at the baseline recruitment and at 6, 12, and 24 months later. Interviewers report all adverse events to their supervisors in real time and identify these as study-related (or not). Serious adverse events (death, criminal acts) are reported to all Investigators, Institutional Review Boards, and funding agencies within 48 h.

At the time of enrollment, interviewers collect detailed locator information from participants, including the names and addresses of friends and family members and favorite hangout spots, locally and in the Eastern Cape, where the ancestral homes of many Cape Town residents are located. The Assessment Team, led by Stellenbosch University, is experienced in using this information to retain participants, consistently maintaining participant retention rates at or above 85% [48].

### Outcome measures

The primary outcome is the NSO out of 15 outcomes, as explained by Harwood et al. [49]. The 15 specific outcomes are explained below, along with how we intend to analyze each outcome. We analyze each outcome separately. We count the number of outcomes out of 15 where the treatment effect is significant at *p* = 0.05 (two-sided) and that count is the NSO. The single NSO outcome allows us to identify the outcomes affected by the intervention while adjusting for multiple comparisons and the correlations among the outcomes. For fifteen outcomes, the NSO needed for a significant result is either 2 or 3 outcomes, depending on the correlation among the outcomes. As a practical matter, the cutoff is 2 only if the correlation among outcomes is near 0 or near 1. For correlations among outcomes between 0.1 and 0.9 (see Table 2 of Harwood et al. [49]), three significant outcomes give significance at the 0.05 level and, based on similar work with similar variables in these same neighborhoods of Cape Town, we plan to require a minimum of three significant outcomes to declare that the treatment is effective.

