#### Fifteen outcomes

We have 15 primary outcomes: 1) Alcohol Use Disorders Identification Test (AUDIT-C) score < 3 (i.e., problematic alcohol use); 2) no alcohol usage in last 24 h; 3) PEth Alcohol Test (excessive alcohol use in prior 3 weeks, at 24 months only); 4) no marijuana (dagga) usage in the last 10 days assessed via RDT; 5) no quaalude (mandrax) usage in the last 2–3 days assessed via RDT; 6) no methamphetamine (tik) usage in the last 1–2 days assessed via RDT; 7) HIV testing in the last 3 months; 8) employment (part/full-time); 9) income above 1200 ZAR/month; 10) no concurrent partnerships; 11) no sex without condoms; 12) no violent acts toward women; 13) no arrests by police; 14) engaged in a community activity; and 15) Center for Epidemiologic Studies of Depression (CES-D) score < 16 (i.e., caseness). Each primary outcome measure is a binary variable (not present or present).

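### The NSO cutoff of three supports only a global claim; it does not identify the affected outcomes with multiplicity adjusted, as the plan says

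*Protocol article*

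**What the plan says.** Under Outcome measures, the protocol article makes the NSO the single primary outcome. The component tests come first: "We analyze each outcome separately". Then: "We count the number of outcomes out of 15 where the treatment effect is significant at *p* = 0.05 (two-sided) and that count is the NSO". On the cutoff, it says: "For correlations among outcomes between 0.1 and 0.9", "three significant outcomes give significance at the 0.05 level". A cutoff of two is said to apply only when the correlation is close to 0 or to 1. The decision rule follows: "we plan to require a minimum of three significant outcomes to declare that the treatment is effective".

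The same paragraph also makes a claim about individual outcomes: "The single NSO outcome allows us to identify the outcomes affected by the intervention while adjusting for multiple comparisons and the correlations among the outcomes". It gives no further step for deciding which individual outcomes are affected. The section Fifteen outcomes opens with "We have 15 primary outcomes" and lists them; they include HIV testing, drug tests, employment, violence toward women and arrests.

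**The concern.** Two different claims rest on one cutoff. One is global: the count is too large to be explained if nothing is affected. The other is specific: these particular outcomes are the affected ones, with multiplicity taken into account. A cutoff that depends only on the number of outcomes and their correlation can be calibrated for the global claim. The specific claim needs control of false findings among the unaffected outcomes when other outcomes do change, and the rule has no such component. True effects bring the count to three, and every other outcome then joins the list if its own unadjusted p-value is below 0.05.

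What is at stake is the list that readers will use. If the trial succeeds, it will report which of 15 quite different behaviours and conditions the programs changed. On the present wording, that list would be described as multiplicity-adjusted when it is not.

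**Working it through.** **Inputs from the protocol article.** 15 outcomes (Fifteen outcomes); 0.05 two-sided per outcome, cutoff three, correlation range 0.1 to 0.9 (Outcome measures); 80% power (sample size paragraph, under Missing data).

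**Assumptions, not in the document.** The test statistics are normal with common correlation r: Z = √r·F + √(1−r)·e, plus a shift for affected outcomes. The number affected, k, is varied. Power per affected outcome is 80% or near-certain (99.99%).

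**Step 1: reproduce the plan's cutoff.** Given F, each unaffected outcome is significant with probability p0(F), so the count under the global null is Binomial(15, p0(F)). Averaging over F gives:

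| r | ≥2, favourable only | ≥3, favourable only | ≥2, two-sided | ≥3, two-sided |
|---|---|---|---|---|
| 0 | 0.053 | 0.006 | 0.171 | 0.036 |
| 0.1 | 0.067 | 0.015 | 0.173 | 0.042 |
| 0.5 | 0.081 | 0.044 | 0.162 | 0.088 |
| 0.7 | 0.071 | 0.047 | 0.142 | 0.095 |
| 0.9 | 0.051 | 0.041 | 0.102 | 0.083 |
| 0.95 | 0.043 | 0.037 | 0.086 | 0.074 |

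Counting favourable results only (0.025 per unaffected outcome) reproduces the stated pattern: three is needed from 0.1 to 0.9, and two is enough near 1 and, within rounding, near 0. The cutoff is therefore a tail probability computed with no outcome affected. The literal two-sided count does not reproduce the pattern in this model. That is a separate matter, but it is why both counting rules are shown below.

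**Step 2: closed form at correlation 0.** Take three outcomes certain to be detected, so the cutoff is met, and 12 unaffected independent outcomes. The chance that at least one of the 12 is significant is:

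- two-sided: 1 − 0.95^12 = 1 − 0.540 = 46.0%
- favourable only: 1 − 0.975^12 = 1 − 0.738 = 26.2%

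**Step 3: the plan's own correlation range.** With a of the k affected outcomes significant, the required probability is the average over F of

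Σ_a Bin(a; k, p1(F)) × P[Bin(15 − k, p0(F)) ≥ max(1, 3 − a)],

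where p1(F) is the chance that an affected outcome is significant. This is the chance that the rule fires and at least one unaffected outcome is significant:

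| Scenario | r = 0.1 | 0.3 | 0.5 | 0.7 | 0.9 |
|---|---|---|---|---|---|
| 3 affected, near-certain, two-sided | 45.1% | 39.7% | 31.9% | 23.2% | 13.5% |
| 3 affected, 80% power, two-sided | 41.0% | 35.1% | 27.2% | 18.6% | 10.5% |
| 5 affected, 80% power, two-sided | 38.9% | 33.8% | 26.4% | 18.1% | 9.9% |
| 8 affected, 80% power, two-sided | 29.7% | 26.7% | 21.8% | 15.4% | 8.6% |
| 3 affected, near-certain, favourable only | 24.3% | 20.2% | 16.0% | 11.6% | 6.7% |
| 9 affected, 80% power, favourable only | 13.6% | 12.2% | 10.4% | 8.2% | 5.4% |

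The 2-df chi-square named under Data analysis gives nearly the same values as two-sided counting.

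**Step 4: one case that needs no model.** If exactly two outcomes change, a count of three requires at least one unaffected outcome to be significant. How often that happens does depend on the model: at 80% power and two-sided counting, about 36% of trials at correlation 0 and 26% at 0.5.

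**Step 5: with a naming step added.** Holm across the 15 p-values after a positive NSO was simulated for 2, 3, 5 and 8 affected outcomes, two-sided, with shifts of 2.8 and 4 standard errors (about 80% and 98% power) and correlations 0 to 0.9. At least one unaffected outcome is named in about 1% to 5% of trials. With five affected at 80% power each, the average number of affected outcomes confirmed falls from 3.9 to 2.3.

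**The case against.** The strongest reply is that the only decision rule in the document is global. Three significant outcomes declare the treatment effective, in line with the overall hypothesis at the end of the Background. No sentence says that every outcome with p < 0.05 will be named as affected. The method is referred to a cited paper, and a reporting rule may sit in an analysis plan that is not shown. This stands as far as it goes: the global decision is not touched by this point. It does not rescue the sentence, which positively claims a property that the described rule lacks.

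A reader might go further and infer any of three things that the documents do not support.

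- **A fixed error rate of 26% to 46% in place of a promised 5%.** Both ends come from step 2, which takes correlation 0, whereas the plan applies the cutoff of three to correlations 0.1 to 0.9. Over that range the rate can be far lower. The 5% level is stated for the NSO result, not for the list of named outcomes.
- **That the list will probably contain a false entry.** With three or more affected outcomes the chance does not exceed 46% in any case run, and it is smallest when benefit is broad.
- **That the rate always exceeds 5%.** It does for three to nine affected outcomes under either counting rule. With favourable-only counting it is about 5% or below for one affected outcome at correlation 0 or 0.9, and 4.2% for twelve affected at 0.9.

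**Conclusion.** The concern holds as a wrong statement about what the primary analysis delivers. A positive NSO licenses the conclusion that at least one of the 15 outcomes is affected. It does not adjust the naming of any particular outcome, and it does not show that three are affected.

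The size depends on the number of outcomes affected, their correlation, their power and the counting rule. It is largest when few outcomes change and the correlation is low. It shrinks when many change, when the correlation is high, or when only favourable results count. All these figures assume equal correlation and normal test statistics. The conclusion that the cutoff gives control only under the global null needs neither assumption.

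**What to change.** Under Outcome measures, delete the claim that the NSO identifies affected outcomes with multiplicity adjusted. State instead that a positive NSO supports only the global conclusion, and that individual outcomes with p < 0.05 are unadjusted and exploratory, reported with estimate and interval. This costs wording only; the NSO decision and its power do not change.

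If the sponsor wants to name individual outcomes with adjusted error control, add a step-down test such as Holm, or a closed test, across the 15 p-values after a positive NSO. It uses p-values that are already computed. The price is the shorter confirmed list shown in step 5. That trade-off is the sponsor's choice; the wording change alone resolves the error.

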### Data monitoring

We formed an independent Data Safety Monitoring Board, comprised of four consultants with substantial research experience in South Africa and the United States. The DSMB meets twice annually and reviews interim analyses after each round of follow-up data collection at 6, 12, and 24 months. Stopping the trial will occur only if there appears to be iatrogenic effects associated with men meeting in groups and exacerbating each other’s risk acts. In particular, we monitor criminal acts, sexual risk, and increased substance use that could be associated with the intervention at the 6- and 12-month interim analyses.

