### Data analysis

Histograms for continuous variables (CES-D, AUDIT-C) will be plotted and screened for outliers and incorrect data and we will build tables for categorical variables, marginally and by treatment condition. Longitudinal data analyses follow the general analysis plan described in detail in Weiss [63]. Longitudinal data will be plotted for continuous variables and empirical summary plots (means ± 2 SE over time, by treatment condition with means and SEs calculated simply at each time point within condition) for all variables.

Neighborhoods and soccer teams are nested within condition; we will use hierarchical regression models with random effects for neighborhood, team within neighborhood, and young men. However, for many outcomes, one or other of the random effects variances will likely be small. Traditional maximum likelihood (ML) software has trouble fitting random effects models when random effect variances are modest or small. However, it is important to include these random effects in the model and to have non-zero variance estimates to properly assess the evidence in the data about the conditions, no matter the size of the variances. Working with SAS or Stata and having to specially adapt models to every outcome due to ML neighborhood and team variance estimated as zero is expensive. The simple but flawed solution of setting the variances to zero causes *p* values comparing conditions to be inappropriately smaller than they merit. In contrast to ML methods, Bayesian methods will not set variance estimates equal to zero, and will properly fit the models we need to our data. We will use the software MCMCglmm [64] or JAGS in R [65], as they both can fit the needed generalized linear mixed models (GLMMs) for discrete and continuous outcomes, estimate all variances appropriately, and run without producing errors, thus saving substantial time and improving the accuracy of the resulting conclusions. To calculate the two degrees of freedom chi-square statistic, we will calculate the posterior mean and covariance matrix of the difference of differences SL-V minus CC, and SL minus CC at 24 months minus baseline and calculate a two degrees of freedom chi square statistic for which we calculate a tail area. The 24-month outcome will be the main time point, with secondary calculations for 6 months minus baseline and 12 months minus baseline.

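### The three-of-15 success rule states neither direction nor arm, and its cutoff fits a signed favourable-only count rather than the joint 2-df test described

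*Protocol article*

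**What the plan says.** In the Protocol article, Outcome measures, the primary outcome is the number of significant outcomes (NSO). The rule is: "We count the number of outcomes out of 15 where the treatment effect is significant at" the two-sided 0.05 level, and "we plan to require a minimum of three significant outcomes to declare that the treatment is effective". On the cutoff, "the NSO needed for a significant result is either 2 or 3 outcomes, depending on the correlation among the outcomes", and "the cutoff is 2 only if the correlation among outcomes is near 0 or near 1". For correlations between 0.1 and 0.9 the article says, citing a table in a methods paper, that three significant outcomes give overall significance at 0.05.

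Data analysis gives the only per-outcome test statistic. It takes the two differences of differences, SL-V minus CC and SL minus CC, each at 24 months minus baseline, and will "calculate a two degrees of freedom chi square statistic for which we calculate a tail area".

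Three other places bear on the point:
- The last paragraph of the Background words the primary hypothesis as an improvement.
- Missing data plans pairwise differences between conditions as estimates, once conditions differ significantly.
- Data monitoring treats harm as a real possibility: "Stopping the trial will occur only if there appears to be iatrogenic effects associated with men meeting in groups".

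**The concern.** A 2-df chi-square is a quadratic form in the two contrasts. It is large when either arm differs from control in either direction, or when the two arms pull apart. If its tail area is what is counted, a significant increase in arrests, drug use or violence adds one to the NSO just as a decrease does. Three outcomes could also reach significance through different arms, yet the rule returns one statement about a single treatment.

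The cutoff is tied to the same question. How many of 15 results are needed to hold 5% overall depends on whether each outcome contributes a 5% event (any significant result) or a 2.5% event (a favourable one). At stake are the meaning and the type I error of the trial's one primary decision.

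**Working it through.** **Inputs.** From Outcome measures: 15 outcomes, a per-outcome level of 0.05 two-sided, a cutoff of 3, a claimed overall level of 0.05 for correlations 0.1 to 0.9, and a cutoff of 2 near 0 or 1. From Data analysis: a 2-df test on two contrasts, critical value 5.991. Assumed, because the article gives no correlation: jointly normal test statistics with a common correlation.

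**Step 1: independence, exact binomial.** P(NSO ≥ 2) = 1 − (1−p)^15 − 15p(1−p)^14.
- Any significant result counts, p = 0.05: 1 − 0.463 − 0.366 = 0.171. P(NSO ≥ 3) = 0.036.
- Only favourable results count, p = 0.025: 1 − 0.684 − 0.263 = 0.053. P(NSO ≥ 3) = 0.006.

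The article says a cutoff of 2 can serve near correlation 0. At 0.171 that is impossible if any 5% result counts. At 0.053 it is roughly right if only favourable results count.

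**Step 2: reproduce the stated pattern.** Simulated null probabilities (at least 200,000 draws per correlation):

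| Correlation | Favourable 1-df, NSO ≥ 2 | Favourable 1-df, NSO ≥ 3 | Either direction 1-df, NSO ≥ 3 | Joint 2-df, NSO ≥ 3 |
|---|---|---|---|---|
| 0 | 0.053 | 0.006 | 0.036 | 0.036 |
| 0.1 | 0.068 | 0.014 | 0.042 | 0.042 |
| 0.17 | 0.074 | 0.022 | 0.050 | 0.050 |
| 0.3 | 0.081 | 0.033 | 0.068 | 0.067 |
| 0.5 | 0.080 | 0.044 | 0.088 | 0.088 |
| 0.7 | 0.071 | 0.048 | 0.095 | 0.096 |
| 0.9 | 0.051 | 0.041 | 0.082 | 0.084 |
| 0.95 | 0.043 | 0.037 | 0.074 | 0.075 |

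The two favourable-only columns give the article's pattern: 2 is not enough from 0.1 to 0.9, becomes enough near 1, is marginal at 0, and 3 always holds 5%. The last two columns do not. There, 3 holds 5% only up to a correlation of about 0.17. For the 2-df test the smallest cutoff that holds 5% is 4 at 0.2 to 0.3, about 4 to 5 at 0.5, 5 at 0.7 and 7 at 0.9.

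**Step 3: unequal correlations.** Outcomes from unlike domains need not share one correlation. P(NSO ≥ 3) for the 2-df test with assumed blocks:
- Five blocks of three: 0.044 (within 0.3, between 0.05), 0.047 (0.3, 0.1), 0.058 (0.5, 0.1).
- Three blocks of five: 0.050 (0.3, 0.05), 0.052 (0.3, 0.1), 0.070 (0.5, 0.1), 0.084 (0.6, 0.2).

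**Step 4: what an unsigned count can do (illustration only).** Effective men per arm: 400 × 0.8 / 1.7284 = 185, from the article's loss to follow-up and design effect. Assumed: correlation 0.3 among outcomes, variance 0.23 per binary outcome, and change-score variance 2 × 0.23 × (1 − r), where r is the within-man correlation of baseline and 24 months.
- r = 0.5 (variance 0.23): if three outcomes worsen by 12 points in both active arms, NSO ≥ 3 has probability 0.56; if five worsen by 14 points, 0.95.
- r = 0.3 (variance 0.322): about 0.39 and 0.82.

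**The case against.** The strongest reply is that the authors mean to count improvements only. The hypothesis speaks of improvement, most outcome definitions code the favourable state as 1, and the cutoff pattern itself matches favourable-only counting. The cited methods paper may say so, and a condensed article may have dropped the phrase. A two-sided level is also natural for a signed contrast and not for a 2-df chi-square, and Data analysis never mentions the NSO. All of this stands as evidence of intent. It does not rescue the rule as written: a 2-df tail area cannot show which results are favourable, and no other per-outcome test is described. Nor does the type I result hang on the 2-df link, since 1-df tests counted in either direction give almost the same error.

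The second reply is that the 5% claim may hold in practice. This stands in part: at low correlations, and in weak block structures, it does.

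Third, pairwise estimates will show arm and sign, each outcome is analysed separately, and the monitoring board watches criminal acts, sexual risk and substance use at 6 and 12 months. That is also true, but none of it enters the success rule.

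A reader might infer that the trial intends to call harm a success, or that it could never tell which arm worked. The documents support neither. The wording permits the first without intending it, and the planned pairwise differences address the second descriptively.

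**Conclusion.** The stated cutoff and the stated test do not fit each other. The missing direction and the missing arm follow from the text and need no assumption about correlation, apart from the inference that the 2-df statistic is what the NSO counts.

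The size of the type I problem does depend on correlation. Under equicorrelation, counting 2-df or either-direction results with a cutoff of 3 gives about 0.04 at 0.1, 0.05 near 0.17, 0.088 at 0.5 and a peak near 0.096 at 0.7. The claimed 0.05 therefore fails over most of the 0.1 to 0.9 range for which it is asserted. Modest block structures give about 0.044 to 0.06, and the strongest one tried gave 0.084. A flat statement that the rule fails to hold 5% would go too far, because the article does not report the actual correlation.

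The harm probabilities in the illustration rest on assumed effects, variance and within-man correlation. They show what the wording allows and are not a forecast.

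**What to change.** 1. Compute the NSO separately for SL-V versus CC and SL versus CC, from the signed 1-df contrasts at 24 months minus baseline. These pairwise differences are already planned.
2. Count an outcome only when it is significant at two-sided 0.05 and favours the intervention. Keep the cutoff of 3 per contrast; the null probability is then at most 0.048 at every common correlation tried.
3. Report significant harmful outcomes in a separate list.
4. Prespecify an allowance for making two arm-versus-control claims. Without one, the chance of at least one false claim is bounded only by 2 × 0.048 = 0.096. The method is the sponsor's choice. One option is to derive the cutoff by re-randomising conditions within triads, which also avoids assuming a correlation. A fixed order of the two comparisons is another, at the cost that the second arm cannot be claimed if the first fails; the article gives neither arm priority.
5. If the joint 2-df test is kept, use it as a descriptive overall comparison outside the success rule.

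The cost is revised wording and a small simulation or permutation program, settled before the 24-month comparison is run. No new data are needed. The favourable-only count is conservative at low correlation (0.014 at 0.1), so some power is given up there; a re-randomisation cutoff could recover part of it.
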